**Methods/Design:**

A prospective therapeutic exploratory, non-placebo controlled, two stage monocenter trial in a total of 29 liver transplant patients was designed to assess the safety and efficacy of *de-novo *CNI-free immunosuppression with basiliximab, mycophenolate sodium, prednisolone and everolimus. The primary endpoint is the rate of steroid resistant rejections. Secondary endpoints are the incidence of acute rejection, kidney function (assessed by incidence and duration of renal replacement therapy, incidence of chronic renal failure, and measurement glomerular filtration rate), liver allograft function (assessed by measurement of AST, ALT, total bilirubin, AP, GGT), treatment failure, (i. e., re-introduction of CNI), incidence of adverse events, and mortality up to one year after OLT.

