### Objectives and endpoints

The primary objective of this pilot study is to evaluate the safety and to investigate the preliminary efficacy of a CNI-free immunosuppressive *de-novo *regimen in patients with impaired renal function undergoing liver transplantation. The primary endpoint was thus defined as the incidence of biopsy proven steroid resistant acute rejection(s) within the first 30 days.

Secondary objectives of the trial are the assessment of adverse reactions and renal function under the proposed study regimen. Secondary endpoints will be evaluated after in one interim analysis and after the end of the follow-up period, i. e., one year, and include mortality, the incidence of infection, treatment failure (defined as re-introduction of CNI), wound-healing disturbances, hepatic artery stenoses, and hemato-lymphatic side effects. Furthermore kidney damage will be assessed by the incidence and length of renal replacement therapy and the estimation of renal function using the Modification of Diet in Renal Disease (MDRD) formula. Finally liver allograft function will assessed by measurement of liver enzymes, bile excretion, and coagulation assays.

All end-points will be compared to reference values of CNI based immunosuppression obtained from a meta-analysis [25].

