### Statistical analysis plan

The confirmatory analysis will be performed for the per-protocol population. All statistical analyses will be performed with a type I error *α *= 0.05 and, where appropriate, a non-inferiority margin of *δ *= -0.1 will be assumed.

All rates will be tested in an approximate one sample design test for non-inferiority [27] against reference values obtained from a pooled meta-analysis of trials with immunosuppressive regimen based on CNI [25].

Confidence intervals will be calculated by the method of Agresti and Coull [28]. The only confirmatory analysis will concern the primary endpoint; all other analyses will be exploratory.

Continuous secondary end-points will be compared to reference values with student's T test unless there is considerable evidence for a non-parametric distribution. Event-time data, i. e., time to acute rejection, patient, and graft survival will be estimated by the Kaplan-Meier method.

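### Kaplan-Meier is named for time to acute rejection although death and graft loss compete with it; a cumulative incidence curve would be a free improvement to this exploratory analysis

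*Protocol article*

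**What the plan says.** All references are to the protocol article.

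- **Time-to-event method.** The Statistical analysis plan section assigns one estimator to three endpoints: "Event-time data, i. e., time to acute rejection, patient, and graft survival will be estimated by the Kaplan-Meier method". It states no censoring rule and names no competing-risk method.
- **Rates.** The same section says "All rates will be tested in an approximate one sample design test for non-inferiority" and "Confidence intervals will be calculated by the method of Agresti and Coull". Incidences are therefore treated as binomial proportions.
- **Status.** "The only confirmatory analysis will concern the primary endpoint; all other analyses will be exploratory".
- **Endpoints.** The primary endpoint is the "incidence of biopsy proven steroid resistant acute rejection(s) within the first 30 days" (Objectives and endpoints). In the Abstract, under Methods/Design, "Secondary endpoints are the incidence of acute rejection, kidney function" opens the secondary list, which ends with "incidence of adverse events, and mortality up to one year after OLT".
- **Follow-up and population.** Patients are followed for one year (Methods & Design). Table 1 requires hepatorenal syndrome, eGFR below 50 ml/min and creatinine above 1.5 mg/dL.

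**The concern.** Kaplan-Meier treats a censored patient as still able to have the event later, at the same rate as those who remain under observation. That is reasonable for someone whose follow-up simply ends. It is not for someone who has died, or whose graft is gone: no later rejection of that graft can occur. With these patients censored, one minus Kaplan-Meier estimates the rejection risk in a hypothetical setting without death or graft loss, and it cannot fall below the proportion who actually reject.

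The document itself expects the competing event. Mortality to one year is an endpoint, patient and graft survival stand in the same sentence as rejection, and the Background links renal dysfunction after transplantation to premature death.

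What is at stake is how an exploratory curve is read. The Discussion calls it unknown whether leaving out calcineurin inhibitors raises the risk of rejection. A curve that errs upwards bears on that question, and it may show a different one-year figure from the binomial incidence of the same event.

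**Working it through.** **Inputs.** From the document: 29 patients; follow-up of one year; a reference rate of 12.61% for steroid resistant rejection under calcineurin inhibitors (Sample size calculation), used here only as a low-end value for acute rejection. The document gives no expected one-year acute rejection rate, no mortality and no timing of either. Everything else below is an assumption. For simplicity, death stands for death or graft loss.

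**1. Direction, with 29 patients.** Suppose 8 reject, 4 die without rejection, and follow-up is otherwise complete. The crude incidence is 8/29 = 27.6%, and the Aalen-Johansen estimate at one year is the same.

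- All deaths after the last rejection: Kaplan-Meier = 21/29, so 1 − KM = 8/29 = 27.6%. Excess zero.
- All deaths before the first rejection: 25 remain at risk, Kaplan-Meier = 17/25, so 1 − KM = 8/25 = 32.0%. Excess 4.4 points.

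One minus Kaplan-Meier is never too low, but it can be exactly right.

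**2. Size over an assumed range.** Let R be the one-year cumulative incidence of rejection and D that of death before rejection. With constant hazards over one year:

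- total cumulative hazard L = −ln(1 − R − D)
- rejection part L_R = L × R/(R + D)
- 1 − KM = 1 − exp(−L_R)

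For R = 0.30 and D = 0.10: L = −ln(0.60) = 0.5108; L_R = 0.5108 × 0.75 = 0.3831; 1 − KM = 0.318, an excess of 1.8 points.

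A second pattern puts 80% of the cumulative rejection hazard in the first three months and keeps the death hazard constant. The standard error is √(R(1 − R)/29).

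| R | D | 1 − KM, constant | 1 − KM, early rejection | Excess (points) | SE (points) |
|---|---|---|---|---|---|
| 12.61% | 5% | 12.95% | 12.77% | 0.2 to 0.3 | 6.2 |
| 20% | 10% | 21.2% | 20.5% | 0.5 to 1.2 | 7.4 |
| 30% | 10% | 31.8% | 30.9% | 0.9 to 1.8 | 8.5 |
| 30% | 15% | 32.9% | 31.4% | 1.4 to 2.9 | 8.5 |
| 40% | 15% | 44.1% | 42.0% | 2.0 to 4.1 | 9.1 |

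With D from 5% to 15% the excess runs from 0.2 to 4.1 points. Every value is below its standard error.

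**3. Extreme cases.** Take 40% and 30% as net one-year risks of rejection and death (each as if the other could not occur), with 40% of the rejection risk and 60% of the death risk in the first 30 days. Hazards are constant within each period.

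- Days 0–30: rejection hazard −ln(0.84) = 0.1744; death hazard −ln(0.82) = 0.1985; event-free at day 30 = 0.84 × 0.82 = 0.6888. Incidence = 0.1744/0.3728 × (1 − 0.6888) = 0.1455.
- Days 30–365: rejection hazard −ln(0.60/0.84) = 0.3365; death hazard −ln(0.70/0.82) = 0.1582; event-free at one year = 0.60 × 0.70 = 0.42. Incidence = 0.3365/0.4947 × (0.6888 − 0.42) = 0.1828.
- Cumulative incidence = 0.328; 1 − KM = 0.400; excess 7.2 points.

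This is the top of a range that starts at 0.6 points (rejection 20%, mortality 10%, 70% of rejections and 30% of deaths in the first 30 days). The top implies a net death risk of 0.30 × 0.60 = 18% by day 30.

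If 40% and 30% are instead read as cumulative incidences in the constant-hazard model of step 2, 1 − KM is 49.7%, an excess of 9.7 points. With early rejection it is 44.7%, an excess of 4.7 points. Nothing in the document supports rates of this order.

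**4. What is unaffected.** The stated two-stage design (more than 7 of 9, then more than 26 of 29; 0.80 versus 0.95) reproduces exactly: type I error 0.0486, power 0.8024. It rests on a 30-day binomial count and does not use the Kaplan-Meier curve.

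**The case against.** The strongest reply is that the plan already yields the right quantity. Acute rejection is a secondary endpoint as an incidence, and incidences are handled as binomial rates with Agresti-Coull intervals. A crude proportion counts a patient who dies without rejection as not having rejected. With complete follow-up it equals the Aalen-Johansen value at one year. This stands, and it limits the harm. It does not remove the point: the report would then carry a curve and a proportion for the same event that can differ for no clinical reason.

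Second, the article does not say that deaths are censored, and a condensed article may leave such a rule to the full protocol. That is correct, so the point is conditional. Censoring is nevertheless the ordinary reading, because the endpoint is time to acute rejection rather than rejection-free survival, and the estimator itself is a stated choice.

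Third, the bias is usually smaller than the sampling error with 29 patients. That also stands. But a wide interval is no reason to keep an error of known direction that costs nothing to remove.

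Two stronger readings are tempting and not supported:

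- **A reader might infer that the curve will inflate the phase III sample size.** The Abstract and Discussion speak only of exploratory data and effect size estimates in general. The one incidence that the Discussion names is steroid resistant rejection.
- **A reader might infer that steroid resistant rejection is also estimated by Kaplan-Meier.** The sentence lists only acute rejection, patient survival and graft survival.

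**Conclusion.** The point holds as a low-severity improvement. The plan names Kaplan-Meier for an event that death and graft loss prevent, in a cohort followed for one year with mortality as an endpoint. If those patients are censored, one minus Kaplan-Meier overstates the cumulative incidence of acute rejection whenever a death or graft loss precedes a later rejection, and not otherwise.

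The size rests wholly on assumed rates: about 0.2 to 4 points with 5% to 15% deaths and 12.61% to 40% rejection, against a standard error of 6 to 9 points. The 7-point and larger figures come from corner cases and should not be quoted as an expected bias.

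Nor should the point be read as a threat to the trial's main conclusion. By the plan's own words the analysis is exploratory. The 30-day primary endpoint, the two-stage rule, alpha, power and the 29 patients do not depend on it.

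**What to change.** In the Statistical analysis plan section, separate the three endpoints. Estimate time to acute rejection by the Aalen-Johansen cumulative incidence function, with death and graft loss without prior rejection as competing events. Keep Kaplan-Meier for patient survival and for graft survival, and say whether death counts as an event in the latter.

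With complete follow-up, the curve at one year will then agree with the binomial incidence of acute rejection.

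The cost is one line of text. Dates of rejection, death and graft loss are already needed for the planned analyses, so no new data, patients or design changes are required.

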## Discussion

Long term kidney damage after OLT in patients with pre-operative renal dysfunction is a growing problem in the MELD era. CNI, which are the basis of most immunosuppressive regimens, may aggravate the damage and should thus be avoided. Reducing or delaying CNI is safe and reduces renal impairment. But it is not known if complete abdication of CNI may increase the risk of rejection.

Before conducting a controlled, randomized, double-blind phase III study to show efficacy of the drug regimen safety has to be ensured. Also effect size estimates have to be obtained for for planing such a study, e. g. for sample size calculation.

Hence, we designed this pilot study as a two-stage, single-group, uncontrolled trial to assess the incidence of steroid resistant rejection under the proposed treatment. If the phase II study corroborates safety of *de-novo *CNI-free immunosuppression the exploratory data may serve as a fundament for planing and conducting a randomized, prospective, controlled double-blinded clinical trial to confirm the results.
